## Abstract

**Introduction:**

Few biomarkers can be used clinically to diagnose and assess the severity of depression. However, a decrease in activity and sleep efficiency can be observed in depressed patients, and recent technological developments have made it possible to measure these changes. In addition, physiological changes, such as heart rate variability, can be used to distinguish depressed patients from normal persons; these parameters can be used to improve diagnostic accuracy. The proposed research will explore and construct machine learning models capable of detecting depressive episodes and assessing their severity using data collected from wristband-type wearable devices.

**Methods and analysis:**

Patients with depressive symptoms and healthy subjects will wear a wristband-type wearable device for 7 days; data on triaxial acceleration, pulse rate, skin temperature, and ultraviolet light will be collected. On the seventh day of wearing, the severity of depressive episodes will be assessed using Structured Clinical Interview for DSM-5 (SCID-5), Hamilton Depression Rating Scale (HAMD), and other scales. Data for up to five 7-day periods of device wearing will be collected from each subject. Using wearable device data associated with clinical symptoms as supervisory data, we will explore and build a machine learning model capable of identifying the presence or absence of depressive episodes and predicting the HAMD scores for an unknown data set.

**Discussion:**

Our machine learning model could improve the clinical diagnosis and management of depression through the use of a wearable medical device.

**Clinical trial registration:**

[https://jrct.niph.go.jp/latest-detail/jRCT1031210478], identifier [jRCT1031210478].

## Introduction

Currently, few biomarkers can be used clinically to diagnose and assess the severity of mental disorders (1, 2). Blood samples, radiographs, computed tomography (CT), nuclear magnetic resonance imaging (MRI), and numerous other tests are used in psychiatry, but these tests are performed primarily to rule out organic and symptomatic mental disorders. Examinations performed purely for psychiatric diagnostic purposes or as adjuncts to such tests include spinal fluid examinations for meningitis and encephalitis, electroencephalography for the diagnosis of epilepsy, cerebral blood flow scintigraphy and cerebral dopamine transporter scintigraphy for the diagnosis of dementia, and near-infrared spectroscopy (NIRS) for the diagnosis of depression, bipolar disorder, and schizophrenia. However, these examinations represent only a small part of the overall field of psychiatry; in general clinical practice, emphasis continues to be placed on medical interviews. Under these circumstances, when using operational diagnostic criteria such as the Diagnostic and Statistical Manual of Mental Disorders (DSM-5), the diagnosis of a disease is based on the patient’s subjective information, such as medical history, symptoms, and the presence or absence of disturbances in daily life. In addition, the severity of the disease is evaluated based on the patient’s or the evaluator’s own subjectivity using a rating scale. However, such symptom evaluation and diagnoses are not objective, and a large range of variation can exist depending on the judgments of medical professionals, which is a major problem in the field of psychiatry (3, 4).

In recent years, studies using accelerometer-equipped actigraphs have been conducted to quantify sleep disturbances and decreased activity levels that often occur in patients with mental disorders (5, 6). Since the presence of insomnia and decreased activity are known to be risk factors for depression (7, 8) and since it has been suggested that activity and sleep measurements are useful for the assessment and monitoring of mental disorders (9, 10), the quantification of these factors could enable risk detection and severity assessments for depression (11, 12). However, many of the existing studies examining actigraphic monitoring of depressed patients have not collected adequate information on disease severity and treatment status and have not been able to determine the risk of depression or to assess the severity of depression in individual patients (13).

On the other hand, the latest wearable devices are capable of previously unavailable measurement modalities, such as heart rate, respiration rate, skin temperature, and location, in addition to actigraphy functions similar to those used for research, and research on depression is now being conducted using these new devices (14, 15). Our research group previously conducted a study to construct a machine learning model using XGBoost to predict the presence of depression and the severity of depressive symptoms by collecting data from 45 patients with depression and bipolar disorder and 41 healthy subjects who were asked to wear a wearable device (16). The study collected data on seven items (acceleration, pulse rate, skin temperature, ultraviolet light, number of steps, energy expenditure, physical activity, and sleep duration) for 5,250 days. In this manner, a model to predict the presence of depression with an accuracy of 76% and a model to predict Hamilton Depression Rating Scale (HAMD) scores (a rating scale for depressive symptoms) with a correlation coefficient of 0.61 were constructed (16). Although these results were preliminarily based on a limited number of subjects, we believed that this machine learning approach could reach a clinically useful level once more data had been accumulated. In addition, since other previous studies have shown that heart rate variability is useful for identifying mood changes and depression (17, 18), the learning model might be further improved by the addition of this parameter.

In the presently proposed study (SWIFT study: SoftWare development Integrating wearable technologies for Future depression Treatment), which is funded by the Japan Agency for Medical Research and Development (AMED), we plan to construct a machine learning model to detect depressive episodes in subjects with depressive symptoms and to quantify the severities of such episodes. This research aims to develop software capable of being certified as a medical device in Japan by increasing the number of samples and improving the accuracy of the model to be built, compared with models produced in previous studies. The model developed in this study is expected to be widely used in commercially available wearable devices, which could then be used by psychiatrists as a basis for making diagnostic decisions and by non-psychiatric clinicians and occupational physicians as a basis for referrals to psychiatrists.

### Research objectives

The general objective of this study is to build a machine learning model that can be implemented as software in a wearable device to detect depressive episodes in subjects with depressive symptoms and to quantify the severities of such episodes. Our specific objectives are: (1) to obtain triaxial acceleration data, pulse rate, skin temperature, and ultraviolet light data from patients with depressive symptoms and from healthy subjects who have been asked to wear a wristband wearable device; (2) to make diagnoses using the Structured Clinical Interview for DSM-5 (SCID-5) and severity assessments using HAMD and to correlate these diagnoses with the collected data; and (3) to construct an optimal learning model enabling the detection of depressive episodes and the evaluation of depressive episode severity by applying machine learning to the collected data set.

## Methods and analysis

### Trial design and setting

This study will be an open-label observational study. Patients who meet the inclusion criteria will be recruited at the time of their outpatient visit to Keio University Hospital or other medical facilities or during their hospitalization, and healthy individuals without a history of mental illness will be recruited through recruitment advertisements on a website. Patient recruitment will be conducted at the following locations and medical facilities: Tokyo (Keio University, Akasaka Clinic, Oizumi Hospital, Oizumi Mental Clinic, and Tsurugaoka Garden Hospital); Kanagawa (Nagatsuta Ikoinomori Clinic); Fukushima (Asaka Hospital); and Yamagata (Sato Hospital). Other medical facilities may be added depending on the recruiting situation.

In this study, patients with depressive symptoms (depressive disorder, bipolar disorder and related disorders, anxiety disorders, obsessive-compulsive and related disorders, trauma- and stressor-related disorders, dissociative disorders, or somatic symptoms and related disorders) and healthy subjects will wear a wristband wearable device up to five times for 7 days at a time. The timing of the start of the measurement period and the interval between each 7-day cycle will differ for each subject.

### Eligibility criteria

The inclusion criteria for patients shall be as follows: (1) a clinical diagnosis of depressive disorder, bipolar or related disorder, anxiety disorder, obsessive-compulsive or related disorder, trauma-and stressor-related disorder, dissociative disorder, or somatic symptom or related disorder according to the DSM-5 criteria, the presence of depressive symptoms, and an outpatient or inpatient status at Keio University Hospital or another medical facility participating in the study; (2) an age of 18 years or older at the time of consent; (3) confirmation from a psychiatrist that the subject is capable of providing written consent or that a guardian can provide consent if the psychiatrist determines that obtaining consent from the patient will be difficult; and (4) ownership and ability to use a smart phone (iOS 11. 0 or later or Android version 5.0 or later). The inclusion criteria for healthy subjects shall be as follows: (1) no history of psychiatric illness and cooperation with the study on a volunteer basis (after obtaining consent, the M.I.N.I. will be used to confirm that the subject does not have a psychiatric illness); (2) an age of 18 years or older at the time of consent; and (3) ownership and ability to use a smartphone (iOS 11.0 or later or Android version 5.0 or later).

The exclusion criteria for patients shall be as follows: (1) an inability to complete measurements that could affect their medical conditions, as determined by a psychiatrist; (2) the presence of comorbidities that could affect the measurement results, such as paralysis of the upper limbs; and (3) ineligibility for other reasons determined by the principal investigator or sub-investigator. The exclusion criteria for healthy subjects shall be as follows: (1) the presence of comorbidities that could affect the measurement results, such as paralysis of the upper limbs; and (2) ineligibility for other reasons determined by the principal investigator or sub-investigator. Researchers will obtain written informed consent from all the participants. The participants will be able to leave the study at any time.

### Primary outcomes

The primary outcome measures will be the machine-learning algorithm’s estimation of whether the patient meets the DSM-5 definition of a depressive episode and the HAMD machine-learning algorithm’s total score estimate.

### Secondary outcomes

Secondary outcome measures will include the HAMD, Montgomery Asberg Depression Rating Scale (MADRS), Young Mania Rating Scale (YMRS), and Beck Depression Inventory–Second Edition (BDI-II) sub-item scores estimated using machine learning algorithms and the estimated total score of combined scores for multiple items.

### Sample size

In our previous study, we collected 241 datasets over 7 days from 86 patients (45 depressed patients and 41 healthy subjects). In the learning model created using XGBoost, the accuracy of identifying symptomatic depressed patients was 76%, and the correlation coefficient with the 17-item version of HAMD for the severity assessment was 0.61 (16). To improve the accuracy of machine learning, as many datasets as possible should ideally be used. However, to minimize the burden on the research subjects and in consideration of study feasibility, etc., we created a learning curve based on the accuracy of detection models and severity assessment models using various sample sizes from the previous study mentioned above. As a result, about 500 data sets were estimated to be necessary to achieve a rough target of 90% for the detection accuracy of depressive episodes (Figure 1). Additionally, about 650 data sets were estimated to be necessary to achieve a severity assessment accuracy corresponding to a correlation coefficient of about 0.85 between the measured and estimated HAMD values (Figure 2). Furthermore, when the average absolute error from the measured HAMD value was set at three, about 800 data sets were estimated to be necessary (Figure 3). These estimates were based on the results of typical and ideal data collections. For detection purposes, a training data set should ideally contain equal numbers of data sets that meet the criteria for depressive episodes and data sets that do not meet the criteria for depressive; for the severity estimation, the data sets should be evenly distributed across a wide range of severities. In practice, however, symptom severity generally declines during follow-up, even if it was severe at baseline, resulting in a large number of data sets with less severe states. For this reason, the severity of the disease cannot be completely equalized. In the proposed study, we plan to collect data from each research subject for up to five measurement periods, if they are willing to participate. To reach the aforementioned target number of data sets, the numbers of patients with each disorder and healthy controls were determined as follows: 220 patients with depression or bipolar disorder, 40 patients with other psychiatric disorders, and 40 healthy subjects, for a total of 300 patients. However, once the target number of cases or half of the data set has been collected, the accuracy of the detection of depressive episodes and the accuracy of the HAMD-17 estimation will be verified, and the target number of cases will be adjusted upward or downward according to Adaptive Design.

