
**FIGURE 1 F1:**
[figure not shown]
Sample size (X-axis) and classification accuracy (Y-axis).

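### The detection target is overall accuracy, which at an unstated and probably unequal episode share can reach 90% with low sensitivity

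*Protocol article*

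**What the plan says.** Primary outcomes makes the algorithm's estimate of depressive-episode status one of two primary outcomes. The only numerical target for it is in Sample size: "about 500 data sets were estimated to be necessary to achieve a rough target of 90% for the detection accuracy of depressive episodes". The metric is percent correct, as the Figure 1 caption shows: "Sample size (X-axis) and classification accuracy (Y-axis". The starting point is the 76% accuracy of the group's previous study.

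Accuracy appears at two further decision points. Sample size says that detection accuracy will be verified at about the halfway point, and that the target number will then be moved up or down. Statistical methods says that the method giving the highest accuracy will be sought.

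On the mix of data sets, Sample size says of its estimates: "These estimates were based on the results of typical and ideal data collections". It adds that "a training data set should ideally contain equal numbers of data sets that meet the criteria for depressive episodes" as data sets that do not. It then says that severity usually falls during follow-up, "resulting in a large number of data sets with less severe states", so that severity cannot be fully evened out. The Discussion lists an unbalanced sample of the two groups as a limitation, without saying which two groups are meant. Its remedy is to check prediction accuracy during the study and change the number of participants. The share of data sets expected to meet episode criteria is not given.

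**The concern.** Overall accuracy is an average of sensitivity and specificity, weighted by the episode share and its complement. When episodes are the minority, the average is driven by how well non-episodes are recognised, and a high value says little about the episodes themselves. The plan points in that direction without stating how far, and still uses accuracy to set the size, to adapt it and to choose the method.

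Two things are at stake. First, 90% could be reported as achieved while a sizeable share of episodes is missed. The intended uses include use "by non-psychiatric clinicians and occupational physicians as a basis for referrals to psychiatrists", where a missed episode and a false alarm have different consequences, and percent correct counts them alike. Second, accuracy can rise between the start and the interim check only because severity has fallen. Under a rule that allows the target number to go down, that rise could support a smaller study although detection has not improved.

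**Working it through.** **The plan's own figure.** The figure of about 500 data sets cannot be reproduced. It was read from Figure 1, which is not shown in the text at hand, and no curve form or intermediate values are given. The planned sample is consistent with it: "220 patients with depression or bipolar disorder, 40 patients with other psychiatric disorders, and 40 healthy subjects" sum to 220 + 40 + 40 = 300 subjects. At up to five periods each this gives at most 300 × 5 = 1,500 data sets, and 500 needs 500/300 = 1.67 per subject.

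**Inputs.** Target accuracy 0.90 (Sample size, Figure 1). Episode share p: not in the document, so 20% to 50% is assumed. Specificity: not in the document, so 100% and 95% are shown.

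**Formula.** Accuracy = p × sensitivity + (1 − p) × specificity. Solved at the target: sensitivity = [0.90 − (1 − p) × specificity] / p.

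| p | Sensitivity at specificity 100% | Sensitivity at specificity 95% | Balanced accuracy (100% / 95%) |
|---|---|---|---|
| 20% | (0.90 − 0.80)/0.20 = 50% | (0.90 − 0.76)/0.20 = 70% | 75% / 82.5% |
| 30% | (0.90 − 0.70)/0.30 = 67% | (0.90 − 0.665)/0.30 = 78% | 83% / 87% |
| 40% | (0.90 − 0.60)/0.40 = 75% | (0.90 − 0.57)/0.40 = 82.5% | 87.5% / 89% |
| 50% | (0.90 − 0.50)/0.50 = 80% | (0.90 − 0.475)/0.50 = 85% | 90% / 90% |

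If sensitivity and specificity are both 90%, accuracy is 90% at every p.

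**Asymmetry.** With sensitivity at its maximum of 100%, the lowest specificity compatible with the target is (0.90 − p)/(1 − p). At p = 20% this is 0.70/0.80 = 87.5%, against a lowest sensitivity of 50%. At p = 50% both limits are 80%. The smaller the episode share, the less the target protects sensitivity relative to specificity.

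**What the shares mean in this sample.** Patients are 260 of 300 subjects. With equal data sets per subject and no episodes among healthy subjects, p = 20% means 0.20 × 300/260 = 23% of patient data sets in an episode, 30% means 35%, 40% means 46% and 50% means 58%.

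**Effect at the interim check.** Take a classifier with fixed sensitivity 70% and specificity 95%. At p = 50% its accuracy is 0.50 × 0.70 + 0.50 × 0.95 = 82.5%. At p = 20% it is 0.20 × 0.70 + 0.80 × 0.95 = 90%. The change in mix alone carries it to the target.

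**Effect of the stated remedy.** The number of participants does not enter the formula. More or fewer data sets of the same mix leave p unchanged.

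**The case against.** The strongest reply has four parts.

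- The 90% is called a rough target and serves to read a number from a curve. The primary outcomes carry no pass mark. This is correct, and the document does not say that the final model will be judged on 90%. It does fix accuracy as the basis for sizing.
- The word accuracy is used loosely. In Sample size it also covers the HAMD correlation, and in Statistical methods the highest-accuracy phrase covers regression methods, for which percent correct has no meaning. This is fair for severity. For detection, classification accuracy is the only version the document defines, so the interim and selection wording most naturally means that.
- Sensitivity, specificity and AUC may be reported under a full protocol or analysis plan that is not shown. Their absence is therefore not the point. The point is the metric that this document sets for sizing, adaptation and selection.
- The imbalance is acknowledged. That stands, but the remedy offered changes the number of participants, not the mix or the metric.

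Several stronger readings are tempting and are not supported:

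- *That most data sets will be non-episode.* The text says that many will be less severe, and a less severe data set may still meet DSM-5 episode criteria.
- *That a model detecting nothing would meet the target.* This needs an episode share of about 10% or less. That is about 0.10 × 300/260 = 11.5% of patient data sets, which sits poorly with patients who must have depressive symptoms at entry.
- *That the earlier 76% came from a different class mix.* The document gives 45 and 41 subjects for that study, not the episode share among its 241 data sets.
- *That the HAMD targets could be met without skill.* A constant prediction has no correlation with HAMD, so the target of about 0.85 excludes it.
- *That a low positive predictive value in referral use supports the point.* It would need a prevalence the document does not give, and it would be the same with sensitivity and specificity both at 90%.

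**Conclusion.** The concern holds for detection only. Overall accuracy sets the size of the detection model and is, as written, the measure for interim adaptation and method choice. The plan itself expects departure from the balanced mix it calls ideal. If the episode share lies between 20% and 50%, a model at exactly 90% accuracy can miss from one half (20% share) to one fifth (50% share) of episodes at specificity 100%, and from 30% to 15% at specificity 95%.

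These are compatible values, not predictions. They rest on an assumed episode share and on specificity above 90%; a model with both rates at 90% would have no such gap. What is established is that the target, and an adaptation based on it, need not show adequate detection, and that changing the number of participants does not cure this.

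**What to change.** Restate the detection target as a pair, one value for sensitivity and one for specificity, with balanced accuracy or AUC as the single summary. The pair should be the binding requirement: in the table above, balanced accuracy is still 90% at a 50% share with sensitivity of only 80%. State the expected share of data sets in an episode. Use the same metrics instead of percent correct at the interim check and for choosing the classifier. Overall accuracy can still be reported beside them, with the observed episode share. Reporting HAMD error by severity band would be useful but is optional.

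No new data collection is needed to restate the target. The change is more than wording, however: the 500 was read from a curve of classification accuracy, so the curve has to be re-read on the new metrics from the previous study's data. The resulting target or number of data sets may look less favourable. The change is best made before the interim check, because the present metric can move the target number.

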
**FIGURE 1 F1:**
[figure not shown]
Sample size (X-axis) and classification accuracy (Y-axis).

**FIGURE 2 F2:**
[figure not shown]
Sample size (X-axis) and correlation coefficient for the 17-item version of the Hamilton Depression Rating Scale (HAMD) measured values and the estimated values (Y-axis).

**FIGURE 3 F3:**
[figure not shown]
Sample size (X-axis) and mean absolute error for the 17-item version of the Hamilton Depression Rating Scale (HAMD) actual values and estimated values (Y-axis).

